#### Monitoring

In this study, the data will be collected automatically through the Python code base and the Lab Streaming Layer. After each phase, the sensors will be checked for failures, and at the end of each individual trial, the data will be summarized automatically to double-check the start and end of measurements, the number of observations for each sensor, and the number of tracked responses of the Stroop task. These reports will be stored and used for data documentation. Further monitoring and audit are not planned.

#### Adverse event reporting and harms

The safety and well-being of the study participants are a priority throughout the study. Participants will be monitored in person during on-site sessions to ensure their comfort and to allow for immediate communication of any concerns or adverse events, although no adverse events are expected given the nature of the intervention. Listening to music is considered a low-risk activity and is not associated with known physical or psychological hazards. In the unlikely case of an adverse event, the investigator, who is trained in first aid, will provide immediate assistance. Additionally, the study will adhere to the safety protocols and emergency procedures established by the campus, ensuring prompt and appropriate action in case of any unforeseen circumstances. Participants will be informed about the minimal risks associated with the study and will have the opportunity to withdraw at any time. The study does not involve interventions that are invasive or potentially harmful, and no long-term follow-up for safety is deemed necessary. During the trial, we expect the participant to focus on a concentration and attention task, and look at a screen. That can lead to a feeling of tiredness, exhaustion, and might lead to a slight headache. The tasks will be performed under time pressure, so the study participant might feel stressed.

#### Auditing

No formal external auditing is planned for this aggregated N-of-1 trial. Internal monitoring will be conducted by the principal investigator, who is not involved in daily data collection. This includes verifying that all sessions are conducted according to the protocol, data files are complete and correctly labeled, and any deviations are documented. Automated scripts will perform data integrity checks (e.g., sampling rates, missing data) after each session and report the results of those checks.

### Dissemination

2.7

#### Protocol amendments

Any modifications to the protocol that may impact the conduct of the study, the potential benefit or risk to participants, or the scientific validity of the trial (including changes to eligibility criteria, study design, outcomes, analyses, or procedures) will require a formal amendment. Amendments will be documented with a new protocol version number and date, and will be submitted to the relevant ethics committee for approval before implementation. All amendments will also be updated in the trial registry record and in any open repositories where the protocol is hosted. Minor administrative changes (e.g., correction of typographical errors) will be documented in the protocol history but will not require ethics notification.

#### Confidentiality

All participant information will be handled in accordance with applicable data protection regulations. Personal identifiers on the study consent will be stored separately from research data and replaced with a unique study ID. There will be no linking of the participant identities to study IDs. Raw data from the Stroop test and physiological sensors will be stored on encrypted devices and transferred to secure institutional servers. Access to the data will be restricted to authorized study personnel. Anonymized datasets will be used for all analyses and will be made publicly available only in non-identifiable form. All physical documents (e.g., consent forms) will be stored in locked cabinets in restricted-access offices. Data will be retained for a maximum of 3 years after study completion, after which it will be securely deleted or destroyed.

#### Access to data

Only the principal investigator, designated co-investigators, and trained scientific staff will have access to identifiable participant data during the study. All such individuals will receive appropriate training in data protection and confidentiality before handling any data. An anonymized version of the final dataset, along with the analysis code and study materials, will be made publicly available in an open-access repository upon publication of the primary results. Access to identifiable data will not be granted to any third party without explicit consent from the participant and approval from the relevant ethics committee.

#### Ancillary and post-trial care

No ancillary or post-trial care will be provided to participants upon completion of the study. Participants will be informed of this policy before enrolling in the trial. The decision not to offer post-trial care is based on the nature and scope of the study.

#### Dissemination policy

The findings of this study will be submitted for publication in a peer-reviewed open-access journal and presented at relevant scientific conferences. The full protocol, anonymized dataset, and analysis code will be made publicly available via an open repository within 36 months after study completion, under a Creative Commons Attribution (CC BY-NC 4.0) license.

## Discussion

3

This study leverages the N-of-1 trial design to provide a personalized approach to understanding the effects of self-selected music genre on concentration. Unlike traditional group-based studies that average effects across participants, the N-of-1 trial design allows to include a personalized protocol for each participant, the efficient estimation of population-level treatment effects as well as of individual-level treatment effects, thereby addressing the substantial variability in how music influences cognitive performance. Although the effect of music on concentration has been explored in numerous studies, results remain inconsistent and inconclusive, likely due to the high degree of individual variability and differences in study designs. By combining a rigorous N-of-1 trial design with repeated measures, this study contributes to the understanding of personalized cognitive responses.

In this study, the participant can select a music genre of their choice. With that, the study allows adjustment for personal preferences. However, the selection of music genres is broader compared to artist or track choice. While other studies have used white noise, office noise, or speech content as the baseline condition, this study aims to mimic a silent work environment without music or additional noise as a comparator. While the study will be conducted in a separate room on the university campus, the study setup does not guarantee complete silence.

The digital adaptation of the Stroop test is employed as an outcome assessment tool to evaluate concentration. While this test provides a practical and flexible measure, it has limitations, particularly in its lack of heavy standardization within the framework of music and cognitive studies. These limitations should be acknowledged when interpreting results, as they may affect the comparability of findings across similar studies.

The sample size calculation for this study is based on generalized linear mixed model (GLMM). The assumed values are based on pilot testing with limited prior evidence and may not fully reflect the true effect size observed during the study. Further, we powered for a small aggregated treatment effect difference of 95% for the no-music condition and 96% for the music condition, which may not be clinically relevant for all participants. Despite this, the individualized nature of the study allows for meaningful intra-participant comparisons, even in the context of such uncertainties.

In this study, the treatment allocation sequence is randomized separately for each participant. Prior to the experimental period, participants will complete seven practice Stroop tasks: two without a time limit and five with a time limit, to familiarize themselves with the task and reduce learning effects during the intervention periods. Washout phases are included between treatment periods to minimize potential carryover effects.

Based on this design, major sequence effects or carryover are not expected. Nevertheless, residual time-related effects such as learning or fatigue cannot be fully excluded. Therefore, although the primary analysis does not explicitly adjust for treatment sequence, sensitivity analyses will explore the robustness of the results with respect to possible temporal trends.

In summary, this study not only explores a novel personalized approach to understanding the effects of music on concentration but also highlights the importance of individualized methodologies in cognitive research. While acknowledging the limitations of the outcome assessment tool, the study provides a valuable framework for future investigations into personalized cognitive enhancement strategies. In addition to advancing our understanding of how music impacts concentration, the study will contribute to the research community by publishing the collected data online. This open-access dataset could serve as a benchmark for developing and testing statistical methodologies for N-of-1 trials, fostering further advancements in personalized cognitive research. Furthermore, the integration of sensor data in secondary analyses will offer unique insights into the physiological correlates of concentration and the potential influence of music on these multimodal measures. Together, these contributions underscore the study’s potential to inform both theoretical understanding and practical applications in personalized cognitive enhancement.

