**(a) fig1a:**
[figure not shown]
Sample size calculation with fixed $\sigma^{2}=0.05$.

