#### Sample size

We estimated the required sample size (i.e., number of participants) for testing a population-level average difference in the primary outcome (Stroop test, see Section 2.3) between periods of intervention condition (self-selected music) and control condition (no-music) through simulation studies. The simulation was performed in R using lme4, with seed 123 for reproducibility. We assumed a correct answer rate of 95% in the no-music condition and 96% across all self-selected music conditions based on pilot testing of the digital version of the Stroop task. That is, we assumed a difference in correct answer rate between the conditions of 1%. We assumed 150 observations per 180-second period based on an average response rate of 1.2 s per answer. This yielded about 600 observations per participant across all four periods. Corresponding to those values, we simulated data of our binary outcome variable $Y_{ij}$ (0 = incorrect response, 1 = correct response) for patient i at time point j (subsequently numbered throughout all periods) with a generalized linear mixed model (GLMM) using an intercept of $\beta_{0}$, a fixed effect $\beta_{1}$ of treatment $A_{ij}$ (0 = control condition, 1 = intervention) and we assumed a random effect $u_{i}∼N\left(0,\sigma_{u}^{2}=0.05\right)$ for each individual: (1)$$\beta_{0}=\mathrm{logit}\left(0.95\right)$$$$\beta_{1}=\mathrm{logit}\left(0.96\right)-\mathrm{logit}\left(0.95\right)$$$$p_{ij}={\mathrm{logit}}^{-1}\left(\beta_{0}+\beta_{1}\cdot A_{ij}+u_{i}\right)$$$$y_{ij}=\text{Bernoulli}\left(p_{ij}\right)$$

We simulated 5000 series of N-of-1 trials for each of the following number n of participants: n∈[15,16,…,29,30]. We used a fixed treatment effect $\beta_{1}$, random effect $u_{i}$, and the outcome was randomly drawn from a Bernoulli distribution as shown in Eq. (1). The seed was set to ‘123’.

Next, for each n, we analyzed each of the 5000 series of N-of-1 trials using the generalized linear mixed model (GLMM) defined in Section 2.5. For each n, we estimated the power as the ratio of p-values of the Wald z-test for $\beta_{1}$ that were <0.05 across the 5000 series of trials and calculated the 95% confidence interval for the estimated power based on the Monte Carlo error of the estimated power: (2)$${\text{CI}}_{\text{upper}/\text{lower}}=\text{Power}\pm 1.96\cdot \sqrt{\frac{\text{Power}\cdot \left(1-\text{Power}\right)}{5000}}$$

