Fig. 1(a) shows that the estimated power was 80.4% (95% CI: 79.3%–81.5%) with 22 patients and 81.3% (95% CI: 80.2%–82.4%) with 23 patients. In a second step, we iterated over different values of $\sigma_{U}^{2}\in \left\{0.1,0.25,0.5,0.75,1\right\}$ and calculated the corresponding power and its confidence interval. Fig. 1(b) shows that all estimated powers are above the required power of 80%, while only with a standard deviation of $\sigma_{u}^{2}=0.25$ the confidence interval of the power includes 80% (79.7%–81.9%). Hence, we aim for 23 participants in our trial.

On the individual level, assuming 600 available data points, this would allow for the estimation of a treatment effect in the improvement of correct answers from 95% to 96% with a 95% confidence interval width of $2\cdot 1.96\cdot SE\left(\overset{ˆ}{\beta_{1}}\right)=0.117$.

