#### Allocation and blinding

The phases within the study will be randomized within each block (*AB* or *BA*) to minimize the risk of bias when combining the results from the individual trials [32]. The randomization will be independent of previous intervention allocations, and the package *numpy* from *python* will be used.

Due to the nature of the intervention, neither the participants nor the investigators conducting the sessions can be blinded to the assigned condition. The outcome measures are objective and automated, which reduces the potential for assessment bias.

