To assess the robustness of the findings, sensitivity analyses are planned. First, as a non-parametric robustness check, we will perform Fisher’s exact test on aggregated counts of correct versus incorrect responses under music and no-music conditions, which provides a simple benchmark for differences between music and no-music conditions, assuming independence of observations. Next, we will include chronological time in the Bayesian generalized linear mixed model (GLMM) with uninformative priors ($\beta_{i}∼N\left(0,1\right)$), as a proxy for time-varying effects of factors such as fatigue or learning. From the fitted models, we will report odds ratios with 95% credible intervals and compute average marginal risk differences for interoperability.

If a value of $y_{ij}$ is missing (e.g., the participant did not respond within the given time frame), it will count as incorrect and be coded as 0. In the case that multiple consecutive values are missing, the length of the missing data will be reported.

In addition to the population-level estimates, we will estimate individual-level intervention effects by contrasting within-person differences in accuracy between music and no-music conditions for each participant across their trial periods. To illustrate this, we will follow the Independent Bayes Approach (IBA) described in Hoffmann et al. [41], presenting participant-specific estimates, visualizations, and posterior probabilities of benefit where appropriate. These analyses will help to characterize heterogeneity in individual responses to the intervention. For the analysis, we will use aggregated counts of the correct answers of the Stroop task.

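### The primary model omits period although order is randomised within cycles without balancing, so a time trend would shift the music effect by chance and leave its credible interval too narrow

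*Protocol article*

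**What the plan says.** Each participant has two cycles, and the order AB or BA is randomised within each (Trial design; Allocation and blinding). On how the draws relate to one another, the protocol states: "The randomization will be independent of previous intervention allocations". No balancing across cycles or participants is described.

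Eq. 4 in Primary analysis models the log-odds of a correct answer with an intercept, a condition effect β1 and a participant random intercept. It has no term for period, cycle or time. The Discussion confirms this: "although the primary analysis does not explicitly adjust for treatment sequence". A sensitivity analysis adds chronological time to the same Bayesian model, "as a proxy for time-varying effects of factors such as fatigue or learning".

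The Discussion expects no major sequence or carryover effects, citing practice items and breaks, but grants that residual learning or fatigue remains possible. Practice consists of seven items, five of them timed.

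**The concern.** The design blocks on cycle, but the primary model ignores the blocking. If accuracy changes between the first and second period of a cycle, any excess of AB over BA cycles (or the reverse) carries part of that change into the music effect. The model's standard error does not allow for this, because Eq. 4 has nowhere to put a period effect.

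The planned effect is one percentage point, so a modest drift can matter. At stake are the primary estimate and the width of its 95% credible interval in the one randomisation that will be realised.

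**Working it through.** **Inputs from Sample size.** "We assumed a correct answer rate of 95% in the no-music condition and 96% across all self-selected music conditions"; "We assumed 150 observations per 180-second period"; random-intercept variance 0.05; "we aim for 23 participants in our trial". Hence 46 cycles, and 23 × 4 × 150 = 13,800 responses. The planned effect is β1 = logit(0.96) − logit(0.95) = 3.178 − 2.944 = 0.234.

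**Plan's own figure.** The stated power is 80.4% (n = 22) and 81.3% (n = 23). A two-proportion formula with 300 responses per person and condition gives 79.1% and 80.9%. A simulated random-intercept logistic model (2,000 runs) gives 80.4% and 83.2%. All are within 2 points, so the planning figure is reproduced.

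**Order imbalance.** With 46 independent draws, #AB − #BA has SD √46 = 6.78, and P(|#AB − #BA| ≥ 8), that is 27:19 or worse, is 0.302.

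**Shift given the split.** Let d be the fall in log-odds from the first to the second period of a cycle. Music comes first in AB cycles and second in BA cycles, so

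shift in β1 ≈ d × (#AB − #BA)/46.

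For d = 0.3 and 27:19: 0.3 × 8/46 = 0.052, and 0.052/0.234 = 22%.

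**Average over randomisations.** The expected imbalance is zero. Simulated mean bias was at most 0.0014 in every null scenario.

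**Variance the interval omits.** The shift has SD d/√46. Take a linear fall from 95% to 90%:
- change per period: (2.944 − 2.197)/3 = 0.249
- SD of the shift: 0.249/6.78 = 0.0367
- mean model-based SE in simulation: 0.0649
- predicted true SD: √(0.0649² + 0.0367²) = 0.0746
- simulated SD: 0.0746

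With a period factor, the simulated SD and mean SE agree (0.0660 and 0.0668).

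**False-positive rate if an interval excluding 0 is read as a test.** Null effect, n = 23, 1,500 to 4,000 simulated series per setting; ranges are over repeat runs. Monte Carlo SE is about 0.3–0.6 points near 5% and up to 0.8 at 11%. Trend sizes are assumptions.

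| Assumed pattern (log-odds) | Accuracy | No time term | Linear time | Period factor |
|---|---|---|---|---|
| none | 95% | 4.7–4.8% | 4.7% | 4.6–4.7% |
| fall 0.1 per period | 95 → 93.4% | 5.0% | 4.4–5.3% | about 5% |
| fall 0.2 per period | 95 → 91.2% | 7.0–7.8% | 4.4–5.3% | 4.7–5.5% |
| fall 0.3 per period | 95 → 88.5% | 10.8–11.1% | 4.4–5.3% | 4.6–5.2%* |
| period-1 step 0.3 | 93.4%, then 95% | 7.6% | 6.4–6.6% | about 5% |
| period-1 step 0.4 | 92.7%, then 95% | 9.0–10.3% | 6.8–8.1% | 4.7–5.5% |

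*One run of 1,500 series gave 6.2%; larger runs gave 5.1% and 4.6%.

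Improvement of 0.1, 0.2 or 0.3 per period gives 5.4%, 5.6% and 8.3% without a time term. That is mostly less than for a fall, because higher accuracy widens the model's own SE.

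**Does the Bayesian model change this?** Hardly. With prior β1 ~ N(0, 1) and an SE of about 0.082, the data carry weight 1/(1 + 0.082²) = 0.993, so the credible interval is close to the Wald interval simulated here.

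**The case against.** A reader might infer that the protocol expects learning or fatigue. It does not: it says only that they are not ruled out, and it gives practice items and breaks as mitigation. Nor does it say that learning would fall in period 1; that pattern is an assumption.

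A reader might also infer that the primary estimate is biased. Over the randomisation it is not. The shift exists only given the realised split.

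The larger error rates need large trends. A fall of 0.3 per period means losing 6.5 percentage points within one short session. For total linear changes of 1 to 2 points, the rate stays at 5.3–5.4%.

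Type I error is not a stated property of the primary analysis, which reports posterior summaries and credible intervals. The 0.05 threshold, "that were <0.05 across the 5000 series of trials", belongs to the sample-size simulation. The consequence is better described as under-coverage of the credible interval.

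Finally, the plan does not ignore time. The chronological-time sensitivity model, if linear, repairs every linear trend tried. Its functional form is not fixed in the article and may be set elsewhere.

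All of this stands and limits the size of the point. It does not remove it: a sensitivity analysis does not correct the headline interval, and a linear term would leave 6.4–8.1% under a first-period step.

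**Conclusion.** The point holds in a conditional form. The primary model omits a factor that the randomisation blocks on, and the draws leave order imbalance to chance. Any period effect then adds variation that the 95% credible interval does not contain.

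The consequence is negligible for small trends, about 7–8% instead of 5% for a fall of 0.2 log-odds per period or a first-period step of 0.3, and about 9–11% for a step of 0.4 or a fall of 0.3. The protocol gives no trend size, so which row applies is unknown. The rates come from logistic models with person intercepts standing in for the Bayesian fit.

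This is a change that should be made, not a flaw that invalidates the trial.

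**What to change.** Put period, as a four-level factor, in the primary GLMM as a fixed effect, and make the unadjusted Eq. 4 the sensitivity analysis. Settle this before the pooled data are analysed.

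The cost is three parameters and about 2 points of power when there is no trend: 83.2% to 80.9% in one simulation and 82.5% to 80.5% in another, so power stays at about 80%. A third, smaller run showed a loss of 0.6 points. The protocol's own amendment rule covers changes to analyses, so a formal amendment would be needed.

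Optionally, if allocation has not begun, assign ABAB, ABBA, BAAB and BABA in permuted blocks of four across participants. Five full blocks are balanced, and the last three participants leave at worst a 24:22 split. The shift for a 0.3 change is then at most 0.3 × 2/46 = 0.013. This takes a few lines in the randomisation code.

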## Trial registration

This trial is registered at German Clinical Trial Register, identifier DRKS00038295.

## Ethical approval

All participants will provide informed consent, and the study will be conducted in accordance with the Declaration of Helsinki. It was approved by the Ethics Committee of the University of Potsdam, approval number 71/2025.

### Study status

Study recruitment is planned to start in December 2025, with an expected end in March 2026; study completion is expected in July 2026.

